#### Intervention

Subjects in the placebo group received a single dose of 0.9% sodium chloride (8.2 mL) as the placebo, which was administered as a bolus injection intravenously over 5 min at 8 h post-baseline (0 h). Subjects in the intervention group received a single dose of dexamethasone 8.25 mg (2.5 mL) made up to 8.2 mL with 0.9% sodium chloride, which also was administered as a bolus injection intravenously over 5 min at 8 h post-baseline (0 h).

#### Schedule of events

Each subject visited the study site twice, the first time for a screening and consent visit and the second time for a period of 26 h for the study itself. A diagrammatic representation of patient flow through the trial is shown in Fig. 1. A full schedule of investigations, interventions and procedures to be performed at each study visit is shown in Table 2.

**Fig. 1 Fig1:**
[figure not shown]
Participant flow diagram. IMP investigational medicinal product

**Table 2 Tab2:** Schedule of events

Observations and Assessments	Visit 1 – Screening	Randomisation	Visit 2 – Intervention (in hours)																											ET
			T = 0	1*	2	3	4	5	6	7	8	9	10	11	12	13	14	15	16	17	18	19	20	21	22	23	24	25	26	After T = 0
Eligibility confirmation	X																													
Informed consent	X																													
Medical history	X																													
Current medications	X																													
Demographics	X																													
MRI safety questionnaire	X		X																											
Vital signs	X		X		X		X		X		X			X											X		X		X	X
Blood test	X		X								X			X											X				X	
Urine Sample^***^	X		← Collected throughout the study →																											
Randomisation		X																												
Urine pregnancy test (females only)**			X																											
Venous cannulation			X																											
Finger-prick test			X								X			X											X				X	
MRI scan			X							X				X											X				X	
Lake Louise score			X		X		X		X		X			X											X					
Administration of IMP or placebo											X																			
Normoxia at 21% O_2_			X																									X	X	
Hypoxia at 12% O_2_				X	X	X	X	X	X	X	X	X	X	X	X										X	X	X			
Hypoxia at 13.5% O_2_																X	X	X	X	X	X	X	X	X						
Inspired O_2_ and CO_2_			X	← Every 15 mins →									← Every 30 mins →																	
AEs and SAEs			←Monitored throughout participation→																											X
End of study																													X	
Early termination																														X

*AE* adverse event, *ET* early termination, *IMP* investigational medicinal product, *SAE* serious adverse event

* Observations will be conducted +/- 30 mins of the stated hour wherever possible. Any deviations will be recorded on the protocol deviation log

**A urine pregnancy test must be carried out on all female participants at visit 2 (intervention visit) prior to conducting any study procedures

*** Urine will be collected in containers provided throughout the study duration, samples collected will be recorded for volume, prepared and stored at -80°C

#### Visit 1 – Screening

Volunteers were invited to attend University Hospitals Coventry and Warwickshire NHS Trust (UHCW) for screening and enrolment. Screening included baseline observations, a comprehensive health and MRI eligibility questionnaire, a pregnancy test if applicable and baseline blood tests. Consent included entering their personal information into the Health Research Authority’s Over-Volunteering Prevention System (TOPS). Once a potential participant had provided permission, the researcher sent a letter and copy of the participant information sheet to the participant’s general practitioner to inform them of their participation in the study.

#### Visit 2 – Intervention

##### Confirmation of eligibility and safety checks

The interventional study visit took place over 26 h in the MRI suite at UHCW. Any participants failing to meet the eligibility criteria on the day of intervention were withdrawn from the trial. Information on the last urine void time, a Lake Louise Acute Mountain Sickness self-assessment score, venous blood samples and baseline observations were recorded. The first MRI scan was then performed and used for baseline values.

##### Hypoxication

Following the assessment at hour 0, participants experienced 24 h of normobaric hypoxia at specific oxygen concentrations using a hypoxication tent (Everest Summit Hypoxic Generator, Hypoxic Systems, New York). The hypoxication tent is a self-contained structure measuring approximately 2 m (w) × 2.5 m (l) × 1.8 m (h), in which the oxygen levels are tightly controlled. Participants may leave the tent during the intervention, during which time they will wear a mask attached to a portable hypoxicator to make sure the inspired oxygen concentrations are controlled. Participants will continue with normal activities while in the tent, such as eating and sleeping. The time from which the participant begins to inspire hypoxicated air (FiO_2_ 12%) marks the start of hour 1. Subsequent observations were taken on the hour, plus or minus 30 min to allow for any unanticipated delays during the study visit. At hour 25, the participant returned to breathing oxygen at normal atmospheric pressure (FiO_2_ 21%). The hypoxication schedule is shown in Table 3.

**Table 3 Tab3:** Schedule of participant hypoxication

Timeline	Inspired oxygen concentration (FiO_2_)
Baseline	Normal atmospheric O_2_ (21%)
Hours 1–12	12%
Hours 13–21	13.5%
Hours 22–24	12%
Hours 25–26	Normal atmospheric O_2_ (21%)

Three hypoxic generators were used to control the environment. Carbon dioxide build-up was controlled with an air pump (Bair Hugger™, 3M, Berkshire, UK). Air from the tent was pumped through two soda lime scrubbers (Spherasorb™, medical grade soda lime from Intersurgical Ltd, UK, in canisters by Draeger Medical UK Ltd). These were replaced after 12 h.

#### Outcome measures

##### MRI

Sequences performed in the brain have previously been found to produce significant results [3]. This imaging included assessment of the diameter and flow rate within the middle cerebral artery using 3D time of flight and 2D phase contrast MR angiography, respectively. In the present study, whole-brain DWI was used to produce ADC maps to quantify brain oedema. A T1-weighted total brain volume sequence was used to calculate changes in brain parenchymal and cerebrospinal fluid volumes as a result of cerebral oedema. T2*-based susceptibility-weighted imaging identified changes in the deep cerebral venous anatomy and found evidence of venous compression secondary to cerebral oedema. In addition, sequences were acquired to assess the cervical spinal cord volume and the total cord length. The flow rate in the internal carotid artery was measured using 2D phase-contrast MR angiography. The acquisition parameters used for all the MR sequences are given in Table 4.

**Table 4 Tab4:** Technical MRI sequence parameters

Sequence	Purpose	TR (ms)	TE (ms)	Flip angle (°)	FoV (mm)	Matrix	Slice width/slice gap (mm)	Acquisition time	Comment
3D time of flight	Asses diameter MCA	27	5.7	20	210 × 210	384 × 256	1.2/0.0	3 min 10 s	
2D phase contrast	Assess flow in MCA	11	5.2	30	160 × 160	256 × 224	5.0	4 min 7 s	1 slice, 25 phases venc = 120 cm s^− 1^
Diffusion-weighted imaging	Produce ADC maps to quantify brain oedema	13,729	86.2	–	240 × 240	256 × 256	4.0/1.0	5 min 57 s	*b* = 0, 800 and 1000 s.mm^−2^
T1 3D FSPGR	Assess brain and CSF volume	8.5	3.3	12	240 × 180	256 × 256	1.8/0.0	5 min	TI = 400 ms Reconstructed to 0.9 mm slice width
SWI	Changes in venous volume	50.9	23.7	10	240 × 240	320 × 288	2.0/0.0	6 min 41 s	Reconstructed to 1 mm slice width
T2 3D FSE (cube)	Volume of the cervical spinal cord	1250	92.2	–	180 × 180	288 × 288	2.0/0.0	3 min 35 s	Reconstructed to 1 mm slice width
Sagittal T2	Assess total cord length	3406	106.3	–	440 × 440	384 × 288	4.0/0.0	1 min 56 s	Images combined to produce a single image
2D phase contrast	Assess flow in the internal carotid arteries	10.5	4.9	30	160 × 160	256 × 224	5.0	4 min 21 s	1 slice, 25 phases venc = 120 cm s^− 1^

*ADC* apparent diffusion coefficient, *CSF* cerebrospinal fluid, *FoV* field of view, *FSE* fast spin echo, *FSPGR* fast spoiled gradient echo, *MCA* middle cerebral artery, *SWI* susceptibility-weighted imaging, *TE* echo time, *TI* inversion time, *TR* repetition time

##### Blood sampling

Venous blood was taken immediately prior to each MRI scan and haematology and biochemistry markers were measured, including full blood count, renal function, erythrocyte sedimentation rate and levels of C-reactive protein. Serum samples were stored immediately at −80°C for a later GFAP analysis. Finger-prick capillary blood samples for purine assessment were also obtained at these time points.

##### Urine samples

Urine samples were collected and processed for every urine void during the intervention. The samples collected will be a spun down via centrifuge and were stored in a monitored freezer set to maintain temperatures of -70° to -85 °C. Samples were frozen within 1 hour of collection.

##### Clinical assessments

Vital signs were monitored every 2 h between hours 0–11 and hours 22–26. After the MRI scan at hour 0, the scans were repeated at hours 7, 11, 22 and 26. Participants were asked to complete the Lake Louise Acute Mountain Sickness Questionnaire at hours 2, 4, 6, 8, 11, 22 and 26. The Lake Louise score is a validated tool for diagnosing and scoring the severity of AMS [20]. Five questions (headache, gastrointestinal upset, fatigue, dizziness and sleep disturbance) were graded 0 (none) to 3 (severe) by participants. A total score of 3 is considered diagnostic of AMS. A score of 6–9 is considered moderate AMS and a score of 10 or above is considered severe AMS. In this study, the Lake Louise score was used to monitor participants for the development of AMS. If a participant had a score of 6 or above or an increase in total score of 2 or greater from the previous score, then consideration was made about withdrawing them from the study. Inspired O_2_ and CO_2_ were measured every 15 min from hours 1 to 9 and thereafter every 30 min from hours 10 to 24.

##### Preparation, storage and administration of the investigational medicinal product

The investigational medicinal product (IMP) was prepared for administration, labelled and stored in the trust’s aseptic laboratory for a maximum of 24 h prior to the study visit. Dexamethasone must not be stored above 25 °C and cannot be refrigerated or frozen. The study medication was stored in a temperature-controlled box. A temperature log ensured it remained within the acceptable temperature range until use. Any medication found to have breached the specified temperature range was discarded. On the intervention day, a member of the study team collected the prepared IMP for administration to the participants. Participants were randomised to receive a single dose of either the placebo or dexamethasone at hour 8 of the intervention visit. A medical doctor, as delegated by the chief investigator, prescribed and administered the study medication.

#### Statistical analysis

##### Summary of baseline data and flow of patients

Data exploration will include comparing the baseline characteristics of the volunteers in the placebo and dexamethasone groups. For continuous characteristics such as age, we will report the mean, median, range, interquartile range and standard deviation. Differences between the two groups will be compared using the Mann–Whitney *U* test. For categorical data such as gender, we will report the number and percentage of cases in each category. Fisher’s exact test will be used to compare the two groups.

##### Statistical analysis plan

As in Sagoo et al. [3], it thought plausible to assume that the outcomes would be normally distributed. We will assess this assumption using the residuals from models that assume the data are normally distributed. If the residuals are not normally distributed, we will transform the raw data and repeat the normality assumption check.

Ultimately the primary aim of the study is to compare outcomes between placebo and dexamethasone groups at 22 h. The comparisons could be made by performing *t*-tests using data collected at 22 h. This is, however, inefficient and so potentially to increase power, we will include outcome measures for all time points. To account for the correlation among measurements taken from the same volunteer at multiple time points, we will analyse data by fitting linear mixed models. Separate linear mixed models will be fitted for different outcomes. Each linear mixed model will include a fixed term(s) for the time at which a measurement was taken, a fixed term for the treatment group of the volunteer and an interaction term for time and treatment group. The interaction term enables us to make inference for the mean difference between the placebo and dexamethasone groups at different time points. If there is an imbalance of a baseline characteristic, a fixed term for the characteristic will be included in the model. Outcome measurement profiles over time will be assessed first. If the relationship is approximately linear, a linear term for time will be fitted. If not, time will be taken as a categorical variable.

For data taken at 22 h, we will report the estimated mean differences, the 95% confidence interval for the mean differences of the primary outcome measures and *p* values to test the hypothesis that the mean difference is zero. As mentioned previously, because this is a pilot study, the hypothesis will be tested at a 20% significance level. Also, for the same reason, we will not adjust for multiple hypotheses (corresponding to different outcome measures).

The above analysis plan will be used if it is plausible to assume that the data are normally distributed. If a transformation does not achieve normality, we will use non-parametric methods such as the Mann–Whitney U test.

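### With categorical time, the planned mixed model adds almost nothing to a 22 h t-test, because the two pre-dose scans are not used to sharpen the 22 h comparison

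*Protocol article*

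**What the plan says.** All of the following is in the protocol article.

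- **Comparison of interest.** The Statistical analysis plan section makes the arm comparison at 22 h the primary aim. It first considers the simple analysis: "The comparisons could be made by performing *t*-tests using data collected at 22 h". It then moves to a mixed model: "This is, however, inefficient and so potentially to increase power, we will include outcome measures for all time points".
- **Model terms.** Besides time, each model has "a fixed term for the treatment group of the volunteer and an interaction term for time and treatment group". The outcome's own pre-dose value is not named as a covariate, and the arms are not set equal before dosing.
- **Coding of time.** The outcome profiles are inspected first. "If the relationship is approximately linear, a linear term for time will be fitted"; "If not, time will be taken as a categorical variable".
- **Covariates.** "If there is an imbalance of a baseline characteristic, a fixed term for the characteristic will be included in the model". The section on baseline data compares the arms by test: "Differences between the two groups will be compared using the" Mann–Whitney U test for continuous characteristics, and Fisher's exact test for categorical ones.
- **Timing.** From Clinical assessments: "After the MRI scan at hour 0, the scans were repeated at hours 7, 11, 22 and 26". The injection is at hour 8 (Intervention), so the 0 h and 7 h scans precede it.

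**The concern.** The mixed model is justified by efficiency, so it should make the 22 h comparison more precise than the t-test does. Randomisation makes the true arm difference zero at every time before the injection. A model that uses this fact can remove the part of the 22 h variation that a person's own earlier values predict. A model that estimates a separate arm difference at 0 h and 7 h does not use it.

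Power is scarce here. The Sample size section moves to a 20% significance level because most outcomes showed smaller differences than the three in Table 1, and Trial oversight allows recruitment to go on to 30 if the first 20 do not show enough. Two pre-dose scans per person, the second already in hypoxia, could add precision without a further measurement.

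Two modelling choices also depend on the data: linear or categorical time, after looking at the profiles, and covariates, after seeing an imbalance that has no stated threshold.

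**Working it through.** **Inputs.** From the article: 20 participants, taken as 10 per arm; MRI at 0, 7, 11, 22 and 26 h; dose at 8 h; test level 0.20. Table 1 gives differences and SDs of 0.5 and 0.45 (whole-brain ADC) and 1.35 and 1.65 (genu ADC). Assumed, because the article does not say: two-sided tests; Table 1 SDs are SDs of the 22 h value; within-person correlation ρ of 0.3 to 0.9, equal between all times (compound symmetry) unless stated.

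**Step 1, Table 1.** The table states no n. At 10 per arm, a two-sided t-test gives, at α = 0.05/0.10/0.20, 65/77/87% for whole-brain ADC (table: 78/86/93) and 41/55/69% for genu ADC (table: 52/64/77). The table is matched within 0.5 point by a normal approximation with 12 per arm. That mismatch is a separate matter; below, 10 per arm is used throughout.

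**Step 2, categorical time.** Arm by time has a free mean in every cell, so with complete data the fitted 22 h contrast is the difference of the two 22 h cell means. On one simulated complete data set, the model contrast and the raw difference were both 0.64652. With known covariance, the standard error is √(2/10) = 0.447 SD units, as for the t-test, at every ρ tried.

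What remains is a gain in degrees of freedom if a random intercept pools variance over five times:

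df = 1 / { [(1+4ρ)/5]²/18 + [4(1−ρ)/5]²/72 }

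At ρ = 0.5: 0.36/18 + 0.16/72 = 0.0222, so df = 45 instead of 18. For ρ = 0.3, 0.7 and 0.9, df = 66, 30 and 21. At α = 0.20, power goes from 87.4% to between 87.6 and 88.3% (whole brain) and from 69.4% to between 69.7 and 70.5% (genu). Over all three Table 1 outcomes, the gain is about 0.1 to 1.1 points. An unstructured covariance gives none.

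**Step 3, using the pre-dose values.** The variance of the 22 h difference is multiplied by

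- 1 − ρ² with the 0 h value: 0.91, 0.75, 0.51 at ρ = 0.3, 0.5, 0.7;
- 1 − 2ρ²/(1+ρ) with 0 h and 7 h: 0.86, 0.67, 0.42.

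Power is from the noncentral t with noncentrality (difference/SD)/√(2f/10), where f is the factor above, and 18, 17 or 16 df for no, one or two pre-dose values:

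| Power at α = 0.20 (%) | t-test | 0 h: ρ 0.3 / 0.5 / 0.7 | 0 h and 7 h: ρ 0.3 / 0.5 / 0.7 |
|---|---|---|---|
| Whole-brain ADC | 87.4 | 89.6 / 93.5 / 98.3 | 90.7 / 95.4 / 99.3 |
| Genu ADC | 69.4 | 72.3 / 78.2 / 88.8 | 73.9 / 81.6 / 92.7 |

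If correlation instead decays with time (ρ per 11 h), the standard error with both pre-dose scans is 0.439, 0.412 or 0.353. The variance factors are then (0.439/0.447)² = 0.96, (0.412/0.447)² = 0.85 and (0.353/0.447)² = 0.62, so the gain is smaller.

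**Step 4, linear time.** Under compound symmetry, the fitted 22 h difference is a weighted sum of the five observed differences. The mean time is 66/5 = 13.2 and the sum of squares about it is 1330 − 5 × 13.2² = 458.8. The weights are 1/5 + 8.8(t − 13.2)/458.8: −0.053, 0.081, 0.158, 0.369 and 0.446 at 0, 7, 11, 22 and 26 h. Hour 26, after return to normal air, counts more than hour 22.

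- Effect constant from 11 to 26 h: 0.158 + 0.369 + 0.446 = 0.97 of the 22 h effect is recovered.
- Effect present at 11 and 22 h but gone at 26 h: 0.158 + 0.369 = 0.53.

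Over both correlation patterns and ρ from 0.3 to 0.9, the ranges are 0.86 to 0.97 and 0.07 to 0.53. The standard error falls to between 0.334 and 0.434, so power can rise or fall.

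**The case against.** A reader might infer that the model can bring no power gain at all. The article does not support that. Time may be linear, in which case the arm difference is not free at each time. A random intercept adds some degrees of freedom. Withdrawal during the visit is foreseen (Participant withdrawal criteria), and if 22 h values are missing, earlier values inform a mixed model, whereas a 22 h t-test drops those people. The article also says only that power may potentially increase; it states no amount. Table 1 describes pairwise comparisons at 22 h, so no stated power figure is shown to rest on the model. All of this stands, and it limits the point to categorical time with few missing values.

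Nor does the linear option answer the concern. It gains precision by assuming a straight-line arm difference from 0 to 26 h, although the dose comes at 8 h and Table 3 has inspired oxygen going from 21 to 12, 13.5, 12 and back to 21%.

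The size is open to challenge. The article gives no ρ; at 0.3 the gain from the 0 h value is only 2 to 3 points. Table 1 SDs may be SDs of change from baseline. At ρ = 0.7 the SD of the 22 h value would then be 0.45/√0.6 = 0.58 for whole-brain ADC, and power would go from 73 to 91% (whole brain) and from 54 to 74% (genu) with 0 h adjustment. The calculations also treat participants as independent, although those attending on the same day share an arm.

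On covariates, a reader might infer that the baseline tests decide what enters the model. The article does not link the two, and it presents the tests as data exploration. An imbalanced baseline outcome value could also count as a baseline characteristic. Even so, entry would depend on the observed data, with no list or threshold.

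**Conclusion.** The point holds for the categorical branch. With complete data, that model returns the raw 22 h difference and improves on the t-test by about 0.1 to 1.1 power points at α = 0.20. The linear branch does borrow across times, but it can bias the contrast of interest and is chosen after viewing the profiles.

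Using both pre-dose scans would cut the variance of the 22 h difference to 0.86, 0.67 or 0.42 of its value at ρ = 0.3, 0.5 or 0.7. This rests on assumed compound symmetry, and the power figures also assume 10 per arm, two-sided tests and Table 1 SDs that describe the 22 h value. The direction is firm; the size depends on a correlation that the article does not give.

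It would go too far to call the planned analysis invalid. In the categorical branch with complete data, the 22 h contrast is unbiased; what is lost is efficiency, in a study that calls itself a pilot.

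**What to change.** 1. Prespecify categorical time and drop the choice made from the profiles.
2. Set the arm means equal at all pre-dose times (MRI at 0 and 7 h; Lake Louise score from 0 to 8 h, with confirmation that the 8 h score precedes the injection) and estimate arm differences only after dosing. Adjusting the 22 h value for the pre-dose outcome values serves the same end.
3. Replace the imbalance-triggered covariates with a short fixed list, for example sex, which is already used to form the pairs. The baseline comparison can stay descriptive.

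No new measurement is needed. Adjustment costs one or two degrees of freedom, already counted in the power figures above. The change is wording only if no outcome data by arm have been seen. Trial oversight describes a preliminary analysis after 20 participants. If that look has been made, the change must be dated and justified, and the model now in the article kept as a sensitivity analysis.

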**Methods/design:**

D4H is a double-blind placebo-controlled randomised trial assessing the effect of dexamethasone on hypoxia-induced cerebral oedema. In total, 20 volunteers were randomised in pairs to receive either 8.25 mg dexamethasone or normal saline placebo intravenously after 8 h of hypoxia with an FiO_2_ of 12%. Serial MRI images of the brain and spinal cord were obtained at hours 0, 7, 11, 22 and 26 of the study along with serum and urinary markers to correlate with the severity of cerebral oedema and the effect of the intervention.

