#### Randomisation

Once eligibility had been confirmed, participants were allocated to the treatment or placebo group via block randomisation. The participants were randomised in sex-matched pairs and the randomisation sequence allocated participants attending on the same day to the same study arm to prevent unintentional unblinding of participants or investigators during the visit. The randomisation list was generated by computer by a statistician. Except in the case of an adverse event (AE) requiring unblinding, only the statistician who generated the list and the pharmacist are not blinded to study allocation. They are not members of the trial management group.

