#### Trial oversight

Trial oversight is provided by the trial management group. The trial steering committee will meet regularly to review progress and the safety of the study. There is also an independent data management group. The study sponsor, UHCW, is a National Institute for Health Research facility. The study was reviewed after the first two participants to ensure the safety and quality measures were met. After 20 patients had completed the protocol, a preliminary analysis was performed, and if sufficient differences had been seen, the study would have been closed to recruitment. If not, recruitment will continue to 30 patients. All potential AEs, as defined by good clinical practice (AEs, SAEs or SUSARs), were compiled by the trial manager and statistician and reviewed by the sponsor. All Grade IV AEs, all SAEs and all SUSARs were reported to the trial management group within 24 h. Participant information will be held securely at the trial sponsor site until study closeout, when they will be transferred to a third-party storage facility with appropriate security, and fire and flood provisions.

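### Covariates enter the outcome models only when a baseline imbalance is seen, which gives up precision at 22 h and leaves each model to be settled after the allocated data are known

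*Protocol article*

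**What the plan says.** Under Statistical analysis plan, the article fits a separate linear mixed model to each outcome, using all time points as responses. The terms always present are time, treatment group and their interaction. Covariates are conditional: "If there is an imbalance of a baseline characteristic, a fixed term for the characteristic will be included in the model". That section does not say what counts as an imbalance.

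Under Summary of baseline data and flow of patients, the baseline comparison is presented as exploratory: "Data exploration will include comparing the baseline characteristics of the volunteers in the placebo and dexamethasone groups". Besides descriptive statistics, for continuous characteristics "Differences between the two groups will be compared using the Mann–Whitney" U test, and for categorical ones "Fisher’s exact test will be used to compare the two groups". No significance level is attached to these tests, and nothing says that they decide which terms enter the models.

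The trial is small. The Abstract reports that "In total, 20 volunteers were randomised in pairs", and Trial oversight allows for more after a preliminary analysis: "If not, recruitment will continue to 30 patients". Under Randomisation, "The participants were randomised in sex-matched pairs", and "the randomisation sequence allocated participants attending on the same day to the same study arm".

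**The concern.** Whether a baseline variable belongs in the model depends on how strongly it predicts the outcome. A prognostic variable improves precision even when the arms happen to be balanced on it. A variable unrelated to the outcome adds nothing, however unbalanced it is. Under randomisation any imbalance is due to chance, so a between-arm test of baseline data does not address the need to adjust.

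The rule therefore does two unhelpful things. In most trials it leaves out a useful covariate, because most trials show no marked imbalance on it. It also leaves the model for each outcome to be settled after baseline data have been compared by arm. The same section prefers mixed models to *t*-tests at 22 h in order to gain power, so giving up a cheap source of precision runs against the plan's own aim.

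**Working it through.** **Nearest figure in the plan.** The article gives no figure for the covariate rule. Table 1 gives 77% power at α = 0.20 for genu ADC (difference 1.35, SD 1.65). The standardised effect is 1.35/1.65 = 0.82. A two-sample calculation at 10 per arm gives 70.8% (normal approximation) or 69.4% (*t*), so the 77% is not reproduced at that size. The normal approximation at 12 per arm gives 76.5%, but the article does not state that size. This is a separate matter. Here the unadjusted reference is 69–70%.

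**Inputs.** From the article: 20 volunteers, effect 0.82 SD, outcome tests at 20% (taken as two-sided). Assumed: 1:1 allocation (10 per arm), independent volunteers, a normal covariate, covariate–outcome correlation *r* of 0.3, 0.5 or 0.7, and a Mann–Whitney trigger at 5% or 20%.

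**Precision.** In outcome-SD units the standard error (SE) of the unadjusted difference is √(2/10) = 0.447. Always adjusting gives about √(2/10) × √(1 − *r*²) × √(1 + 1/16), where 1/16 = 1/(20 − 4) is the average cost of estimating the slope:
- *r* = 0.3: 0.447 × 0.954 × 1.031 = 0.440 (simulated 0.439)
- *r* = 0.5: 0.447 × 0.866 × 1.031 = 0.399 (simulated 0.396)
- *r* = 0.7: 0.447 × 0.714 × 1.031 = 0.329 (simulated 0.326)

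With a 5% trigger the simulated SE under the rule is 0.444, 0.434 and 0.421. At *r* = 0.7 its variance is (0.421/0.326)² = 1.67 times that of prespecified adjustment.

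**How often the rule acts.** With no systematic difference between arms, the Mann–Whitney test fires in about 4% of trials at a 5% trigger and 19% at a 20% trigger. An observed difference above 0.5 SD corresponds to *t* = 0.5 × √5 = 1.118 on 18 df and arises by chance in about 28% of trials per covariate. Of these, 16% are flagged at 5% (84% missed) and 65% at 20% (35% missed). For a binary characteristic, 3/10 v 7/10 gives Fisher p = 0.18 and 2/10 v 8/10 gives p = 0.023.

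**Power and type I error** (simulated; repeat runs differ by about one point):

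| | *r* = 0.3 | *r* = 0.5 | *r* = 0.7 |
|---|---|---|---|
| Power, never adjusted | 69% | 70% | 70% |
| Power, rule with 5% trigger | 69–70% | 70% | 70–71% |
| Power, rule with 20% trigger | 70% | 71% | 73% |
| Power, always adjusted | 70–71% | 76–77% | 87% |
| Type I error, rule with 5% trigger | 0.197 | 0.186 | 0.180 |
| Type I error, rule with 20% trigger | 0.195 | 0.174 | 0.152 |

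**Hour 0.** Keeping hour 0 among the responses does not fill the gap. With complete data, categorical time and a free time-by-group interaction, the estimated 22 h contrast is simply the difference between the two 22 h means. It is not adjusted for hour 0.

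**The case against.** Four objections deserve an answer.

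*The tests are not stated to be the gatekeeper.* This stands. A reader might infer that non-significance is taken as proof of balance, but the article does not say so, and imbalance could equally be judged from the descriptive statistics. The conclusion does not need that inference. If the tests are the trigger, the rule rests on a p value that is beside the point; if they are not, the choice is open after the data are seen. The remedy is the same.

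*Most imbalances would be picked up.* This depends on a threshold that the article does not give. At 5% most observed differences above 0.5 SD are missed; at 20%, the level used for the outcome tests, most are flagged. The power loss changes little between the two.

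*False positives.* A reader might infer that the rule pushes error above 20%. Overall it does not. Among trials with an unflagged imbalance above 0.5 SD (0.277 × 0.84 = 23% of trials at a 5% trigger), the rate is higher, about 35% at *r* = 0.7. It is about 12% where the imbalance is smaller. Taking about 20% in the flagged trials, 0.23 × 0.35 + 0.72 × 0.12 + 0.04 × 0.20 = 0.175, close to the simulated 0.180.

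*Covariate lists and thresholds belong in a separate analysis plan, and this is a pilot.* The missing threshold alone would not be a finding. But the article states the rule itself, so a fuller plan would have to overturn it rather than fill it in.

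Two limits also stand. The simulation compares a *t*-test with analysis of covariance rather than the full mixed model. And same-day volunteers share an arm, so 10 independent units per arm may be generous.

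**Conclusion.** The point holds as one of efficiency and prespecification. Making adjustment depend on observed imbalance forgoes almost all the precision that a prognostic covariate offers and leaves the model open after allocation is known. At 10 per arm, 0.82 SD and α = 0.20, the loss is about 1 power point at *r* = 0.3, 6–7 at *r* = 0.5 and 14–17 at *r* = 0.7. The correlations are assumptions, since the article reports none. If the available covariates predict the outcomes only weakly, little is lost. The documents do not support a claim of inflated type I error or of systematic bias: chance imbalance does not bias a randomised comparison on average. The change is worth making because it is cheap and the trial is small.

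**What to change.** Replace the conditional sentence in Statistical analysis plan with covariates fixed before unblinding and included in every outcome model whatever the observed balance: sex and the outcome's own hour-0 value. Sex belongs there because it was used in forming the pairs. If a matched pair is the couple attending on the same day, both members share an arm, and the pairing itself does not balance sex between arms.

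State how hour 0 is handled, because the model already takes all time points as responses. Either remove hour 0 from the responses when it is a covariate, or keep it as a response with the two arms' hour-0 means constrained to be equal.

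In Summary of baseline data and flow of patients, describe the arms without using tests to choose covariates. Label any adjustment prompted by an observed imbalance as a sensitivity analysis. Since Trial oversight describes a preliminary analysis after 20 participants, record whether the covariates were fixed before it.

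No new data are needed, since sex and hour-0 measurements are already collected. The cost is one or two degrees of freedom. In simulation a covariate unrelated to the outcome lowers power from 69.1% to 67.6%, or 69.1 − 67.6 = 1.5 points; about 1–2 points per covariate is a fair allowance.
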